#### Missing data

Missing data will be examined to determine if data are missing completely at random (MCAR) or missing at random (MAR). Full information maximum likelihood (FIML) or the multiple imputation (MI) method will be used to estimate missingness and are shown to produce unbiased results. MPlus will be used as it can handle missing data by providing FIML estimation; otherwise, the pattern mixture model framework will be used to conduct data analyses.

### Plans to give access to the full protocol, participant-level data, and statistical code {31c}

Data from surveys will be deposited and made available through the Inter-University Consortium for Political and Social Research (ICPSR), which is an NIH-funded repository 1 year from project completion. These data will be shared with investigators working under an institution with a Federal Wide Assurance (FWA) and could be used for secondary study purposes.

## Oversight and monitoring

### Composition of the coordinating center and trial steering committee {5d}

This is a single-site study, so there will be no coordinating between centers. This trial does not have trial steering committee. However, the PI will meet regularly with the management team, co-investigators, and data and safety monitoring board.

### Composition of the data monitoring committee, its role and reporting structure {21a}

A board comprised of three members experienced in clinical trials and working with vulnerable populations will be convened twice yearly to review safety and progress. Adverse events will be monitored, and whether youths show deterioration as a function of the intervention received will be assessed (e.g., increase in substance use, mental health symptoms). The board will prepare a summary report after each meeting. The report will detail the meeting proceedings and recommend changes to study protocol, if deemed necessary. The board’s summary report and other required data reports on adverse event cases will be submitted to the IRB and our NIDA project officer.

### Adverse event reporting and harms {22}

Adverse events are defined as an event that has not been previously observed or is not consistent in nature, severity, or frequency with existing risk information. Serious adverse events are defined as an adverse event that is fatal or life threatening, permanently disabling, requires or prolongs hospitalization, or results in significant disability, congenital anomaly, or birth defect. Should a client experience a serious adverse event that was unanticipated and believed to be related to study procedures, the OSU IRB and NIDA will be notified within 48 h. Adverse events that are unexpected and related to the study, but not meeting the definition of a serious adverse event, will be reported to the IRB within 10 days of the PI’s discovery of the event. The OSU IRB reviews the adverse event report and determines if the event is a result of study procedures. If the event is considered a direct result of study procedures, the PI and the board will meet within 48 h and will discuss the modifications to the protocol that are needed in order to prevent future adverse events. An adverse event report will be distributed to all board members. After the session, the board will send a summary report to all of the project investigators outlining the board’s recommendations for necessary changes to the protocol based on the adverse event which will then be forwarded to the IRB.

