#### YEH and suicidal risk

Overall, studies estimate that between 20 and 68% of YEH have attempted suicide at least once in their lifetime [5, 6]. This rate is much higher than that observed in the general youth population, for example, the Centers for Disease Control [7] found that 8.9% of youth report a prior suicidal attempt. Among YEH who have attempted suicide, an average of 6.2 attempts is reported. In addition, lifetime suicidal ideation rates have ranged from 14 to 66.5% [8]. Given that suicidal ideation is a robust predictor of suicide attempts, and suicide attempts are likely to be infrequent in the 12-month study period, suicidal ideation was chosen as our primary targeted outcome. However, suicide attempts will also be assessed.

YEH experience trauma both before and after becoming homeless [9] which contribute to suicidal thoughts and attempts [10]. Rates of physical and sexual abuse range between 16 and 60% [11]. Rew et al. [12] found that YEH who had experienced physical or sexual abuse were 1.8–3 times more likely to attempt suicide compared to YEH without abuse histories. Sexual abuse may be particularly influential on suicidal thoughts and behaviors. For example, Kidd [10] found that the impact of physical abuse on suicidal behavior faded once youth left home, while sexual abuse continued to predict suicidality even after youth left their homes. Overall, youth who have experienced childhood abuse are at an increased risk of suicide. However, experiences on the street can also contribute to suicidal behavior among YEH. In particular, sexual victimization (e.g., rape) has been associated with higher rates of suicidal ideation and attempts [8]. Other risks include street victimization, sex trafficking, criminal involvement, and substance abuse [13]. In sum, the lives of YEH are often characterized by violence, chaos, abuse, and neglect prior to and after becoming homeless, which itself has been associated with higher suicide risk.

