### Criteria for discontinuing or modifying allocated intervention {11b}

If the therapeutic is found to cause harm to participants (e.g., increase in suicidal ideation or substance use), the trial will be stopped.

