### Outcomes {12}

Each of the measures below is assessed at baseline, 3, 6, 9, and 12 months in order to determine change over time (Table 1).

**Table 1 Tab1:** Suicide prevention protocol schedule of procedures and assessments

Procedures/assessments	Study period					
	**Allocation**	**Baseline**	**Follow-up**			
			**3 months**	**6 months**	**9 months**	**12 months**
Enrolment:						
Eligibility screen	5 min	X				
Informed consent	5 min	X				
Interventions:						
Service as Usual (SAU)	6 months	X	X	X		
Cognitive Therapy for Suicide Prevention (CTSP) + SAU	6 months	X	X	X		
Assessments						
Locator form	5 min	X	X	X	X	X
Demographic/Homeless Experiences Form (HEF)	10 min	X				
Follow-up Homeless Experiences Form (HEF)	10 min		X	X	X	X
Services contact log	5 min	X	X	X	X	X
The Client Satisfaction Questionnaire (CSQ-8)	10 min	X	X	X	X	X
Scale for Suicide Ideation – Worst (SSI-W)	10 min	X	X	X	X	X
Form 90	20 min	X	X	X	X	X
The Beck Depression Inventory II (BDI-II)	10 min	X	X	X	X	X
Inventory of cognitive distortions	5 min	X	X	X	X	X
The Social Problem-Solving Inventory-revised Short-version (SPSI-R:S)	5 min	X	X	X	X	X
The Coping Inventory for Stressful Situations-Short Form (CISS-SFC)	5 min	X	X	X	X	X
The Distress Tolerance Scale (DTS)	10 min	X	X	X	X	X
The Impulsivity Control Scale (ICS)	5 min	X	X	X	X	X
The Social Network Inventory (SNI)	10 min	X	X	X	X	X
The Interpersonal Needs Questionnaire (INQ)	10 min	X	X	X	X	X
Beck Hopelessness Scale (BHS)	10 min	X	X	X	X	X
Acquired Capability for Suicide Scale (ACSS)	10 min	X	X	X	X	X
WAI (Monthly-5 times)	5 min		X	X		
Cortisol levels	10 min	X	X	X	X	X

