### Interim analyses {21b}

No interim analyses are planned.

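### The adverse event definition admits only unexpected events, and the promised assessment of suicide attempts has no measure or visit, so attempts may go uncounted or be counted unequally by arm

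*Protocol article*

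**What the plan says.** **Definition.** In the section Adverse event reporting and harms {22}, the rule reads: "Adverse events are defined as an event that has not been previously observed or is not consistent in nature, severity, or frequency", the yardstick being what is already known about risk. Serious events are built on that term: "Serious adverse events are defined as an adverse event that is fatal or life threatening", with disability, hospitalisation and birth defect as further criteria. The same section limits 48-hour notification to serious events that are unanticipated and related. It sets a 10-day report for non-serious events that are unexpected and related.

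**Attempts.** The section YEH and suicidal risk explains that ideation is the primary outcome because attempts will probably be rare over 12 months, and then adds: "However, suicide attempts will also be assessed". Under Outcomes {12} the protocol says: "Each of the measures below is assessed at baseline, 3, 6, 9, and 12 months in order to determine change over time". Neither the list that follows nor Table 1 contains an attempt measure. The outcome measures section describes the SSI-W as rating the worst ideation of the previous 90 days.

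**Session checks.** The description of CTSP has suicidal thoughts and behaviours reviewed at each session. The description of SAU mentions standard practice for suicidal ideation but no equivalent check.

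**Board.** Under Composition of the data monitoring committee {21a}: "Adverse events will be monitored, and whether youths show deterioration as a function of the intervention received will be assessed". Increases in substance use and in mental health symptoms are given as examples.

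**The concern.** A rule for recording events should be wider than a rule for reporting them urgently. Here the first has taken the form of the second. In most trials that would lose some minor expected events. In this trial it can lose the most important ones, because attempts are part of the known background risk. The protocol cites lifetime attempts in 20 to 68% of these youth and accepts an attempt in the past year as a route to eligibility. One more attempt by a participant is therefore easily judged consistent with existing risk.

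Two things are at stake. The board and the final report may lack a complete count of attempts and admissions. What is counted may also be counted more fully in one arm, because the trial is unblinded and the only described routine check on suicidal behaviour belongs to the experimental treatment. An incomplete count can hide harm, and an unequal one can create the appearance of it.

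**Working it through.** No stated sample size, power or error rate is in question, so there is no figure to reproduce. The check sets the sections side by side and then adds a scale.

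**1. Does the definition filter on expectedness?** Yes. Both of its limbs (new, or inconsistent with known risk) describe unexpected events. The reporting rules then add unanticipated or unexpected as a further condition. That condition would be redundant if every adverse event already had to be unexpected, which suggests that recording and reporting were merged in drafting.

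**2. Do serious events escape the filter?** No. They are adverse events that meet a severity criterion, so an expected life-threatening event fails at the first step.

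**3. Does the frequency clause rescue it?** Only in principle. An excess in one arm is inconsistent in frequency, but it can be seen only if each single event has already been counted by arm.

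**4. Is there another route for attempts?** Table 1 schedules the SSI-W, Form 90 and BDI-II at all five assessments in both arms. None is described as recording attempts. A services contact log is also scheduled at each assessment and might pick up some admissions, but the article uses it only to classify baseline service connection. CTSP offers 10 + 9 = up to 19 sessions, each with a check on suicidal behaviour. No such check is described for SAU.

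**5. Scale (assumption).** The documents give no 12-month attempt rate, so a range is shown. Inputs from the protocol are N = 300, 150 per arm, and 20% attrition at 12 months, which leaves 150 × 0.80 = 120 per arm.

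Expected attempters = N × rate. Power to see a doubling over the SAU rate p0 (p1 = 2·p0, mean p̄, two-sided 0.05) is

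Φ{[p1 − p0 − 1.96·√(2·p̄(1 − p̄)/n)] / √([p1(1 − p1) + p0(1 − p0)]/n)}.

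For p0 = 0.10 and n = 150: (0.10 − 1.96 × 0.0412)/0.0408 = 0.47, and Φ(0.47) = 0.68.

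| Assumed rate | Attempters of 300 | Per arm | Power, 150 per arm | Power, 120 per arm |
|---|---|---|---|---|
| 5% | 15 | 7.5 | 0.38 | 0.31 |
| 10% | 30 | 15 | 0.68 | 0.58 |
| 20% | 60 | 30 | 0.97 | 0.93 |
| 30% | 90 | 45 | >0.99 | >0.99 |

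At the lower rates, which fit the protocol's own expectation better, even a complete count would miss a doubling quite often. Such a count should be read descriptively, and lost events make it weaker still.

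**6. Unequal capture (assumption).** Observed count = 150 × rate × capture. With a true rate of 10% in both arms, full capture under CTSP gives 150 × 0.10 × 1.0 = 15, and half capture under SAU gives 150 × 0.10 × 0.5 = 7.5. That is a doubling with no true difference. At 75% capture under SAU the counts are 15 and 11.25.

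**The case against.** The best defence is that this is loose drafting in a condensed article. The redundant qualifiers in the reporting rules suggest that expectedness was meant only as the reporting trigger. The severity and frequency wording would admit unusually grave or unusually numerous attempts. Table 1 lists instruments rather than items: the past-year attempt question used for eligibility has no row even at baseline, so a missing row is weak evidence that the question will not be asked again. The background section says outright that attempts will be assessed.

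Part of this stands. The text does not prove that attempts will go unrecorded, and intent may be better than wording. But the definition is a stated rule, not a detail left out, and staff who follow it may leave out expected events. The promise on attempts still has no instrument, visit or arm attached to it.

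A reader might go further and infer three things that the documents do not support.

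- **That stopping for harm has no data behind it.** The stopping statement ("If the therapeutic is found to cause harm to participants") gives increases in ideation and substance use as its examples. Both are measured at every visit in both arms, and the statement is not tied to adverse event counts.
- **That the board would look at empty tables.** Its review of deterioration by intervention is a second stream of information, and the scheduled scales can feed it.
- **That "No interim analyses are planned" contradicts that review.** A plan without interim analyses can coexist with six-monthly safety review. Any harm guideline may sit in a full protocol or board charter that is not shown. The article describes no repeated significance testing by the board, so no false-alarm rate can be attributed to it.

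**Conclusion.** The concern holds in a limited form. The adverse event definition excludes expected events, serious events inherit the exclusion, and the promise to assess attempts is not carried into the schedule or the measures. Attempts, and other expected serious events outside the scheduled scales such as overdoses and psychiatric admissions, may therefore be uncounted or counted unequally by arm. It does not extend to worsening ideation, substance use or depressive symptoms, nor to the primary analysis.

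The size cannot be fixed from the documents. The 15 to 90 attempters and the 15 against 7.5 contrast rest on assumed rates and capture fractions, and the protocol itself expects attempts to be infrequent. The conclusion about the wording depends on none of these figures. This should be fixed, since events not recorded as they occur may be hard to recover later, particularly with 20% of youth expected to be lost by 12 months.

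**What to change.** 1. Define an adverse event as any untoward occurrence after consent, whether or not expected and whether or not related. Define serious events from that wider set. Keep unexpected and related only as the trigger for expedited reporting.
2. Ask the existing eligibility question on attempts at 3, 6, 9 and 12 months in both arms, with recall set to the time since the last completed interview. The eligibility wording looks back a year. At 3 months it would reach 12 − 3 = 9 months before baseline, and an attempt made in the first 3 months could be counted at all four follow-ups.
3. Add the question to Table 1, and state that attempts noted in CTSP sessions do not replace the interview count when arms are compared.
4. Tabulate attempts, hospitalisations and deaths by arm for the board and the final report.
5. Bring the sections on suicidal risk, the CTSP description, Outcomes and Table 1, the data monitoring committee and adverse event reporting into line with these changes.

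The cost is a protocol and IRB wording change, one short question at four interviews, and by-arm safety tables. No extra staff are needed.

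### Between six-monthly meetings, a serious event has a timed route to the safety board only if it is unanticipated, believed related and then ruled a direct result of study procedures

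*Protocol article*

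**What the plan says.** All references are to the protocol article.

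- **Routine review.** Sections {21a} and {23} have the board meet every six months. Section {21a} gives it the comparative task: "whether youths show deterioration as a function of the intervention received will be assessed".
- **Expedited notice.** Section {22} sends notice within 48 hours to the IRB and NIDA, under two conditions: "Should a client experience a serious adverse event that was unanticipated and believed to be related to study procedures". The board is not named as a recipient at this step.
- **Causality ruling.** "The OSU IRB reviews the adverse event report and determines if the event is a result of study procedures". No time limit is given for this ruling.
- **Board involvement.** "If the event is considered a direct result of study procedures, the PI and the board will meet within" 48 hours. At that meeting the PI and the board "will discuss the modifications to the protocol that are needed in order to prevent future adverse events". The next sentence reads "An adverse event report will be distributed to all board members", with no time limit of its own; the text then turns to what follows the session.
- **Definition.** Section {22} counts as adverse only events that are new or out of line with the known risk profile, and serious events are defined as a subset of these.
- **Action on harm.** Section {11b}: "If the therapeutic is found to cause harm to participants (e.g., increase in suicidal ideation or substance use), the trial will be stopped". It names no decision-maker.
- **Interim analyses.** Section {21b} plans none.

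**The concern.** Participants are enrolled because of recent suicidal ideation or a past-year attempt, so a serious suicidal event can easily be classed as expected. A single event of this kind can also rarely be attributed to the therapy, or cleared of it, on its own facts. What can inform the question is the count by arm, and the board is the body given a between-arm safety task. Filtering events by expectedness and individual causality before the board hears of them works against that task.

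At stake is delay. Several serious events in one arm, each judged expected or unrelated, could accumulate between meetings while randomisation continues, without the board having been told under any stated rule.

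A second, smaller matter is what happens once harm is found. One section speaks of stopping the trial; two others speak of changing the protocol.

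**Working it through.** The route to the board is a matter of text. Arithmetic enters only to give the scale.

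**1. Which serious events reach the board between meetings.** Following section {22} in the order written:

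| Serious event | 48-hour notice to IRB and NIDA | Board before next routine meeting |
|---|---|---|
| Judged expected | No | No stated route |
| Unanticipated, not believed related | No | No stated route |
| Unanticipated, believed related, not ruled a direct result | Yes | No timed route |
| Unanticipated, believed related, ruled a direct result | Yes | Meeting within 48 hours |

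Only the last row leads to the board on a clock. I read the direct-result judgement as the IRB's, since that sentence follows straight after the one giving the IRB the ruling. The definition of an adverse event adds to the first row: an event in line with known risk may not count as an adverse event at all.

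**2. Whether another section supplies a route.** Section {5d} says the PI meets the board regularly, but sets no frequency and no event trigger. The sentence on distributing a report to board members carries no deadline, and it sits between the ad hoc meeting and what follows that meeting. Neither gives a timed alternative.

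**3. Scale.** Inputs: 8 youth recruited per month and a total of 300 (section {13}); board meetings 6 months apart (sections {21a}, {23}); equal allocation, 150 per arm (section {8}).

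- Check on the rate: 8 × 12 = 96 per year, which agrees with the 96 baseline assessments in each of years 2 and 3 of Table 2.
- Longest interval: 8 × 6 = 48 youth; 48 / 300 = 16%; about 48 / 2 = 24 of them to CTSP.
- Average interval, if events fall uniformly between meetings: 6 / 2 = 3 months; 8 × 3 = 24 youth; about 12 to CTSP.

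These figures apply while recruitment is open.

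**4. Action once harm is found.** Section {11b} is triggered by a finding that the therapeutic harms participants, and its stated consequence is that the trial stops. Section {22} is triggered by an event resulting from study procedures, and its stated consequence is discussion of protocol modifications. Section {21a} has the board assess deterioration by intervention and recommend protocol changes if needed; increased substance use is its example of deterioration and also one of section {11b}'s examples of harm. The triggers overlap where the harm is attributed to CTSP. For that case no section says which consequence governs or who decides.

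**The case against.** The strongest case on the other side has five parts.

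- **Routine review is unfiltered.** A reader might infer that the board hears only of cases already judged causal. The article does not support that: at its six-monthly meetings the board reviews safety, and section {21a} attaches no relatedness condition. The gate affects what reaches the board between meetings.
- **The definition mentions frequency.** An excess of attempts could therefore be recognised as out of line with known risk. That is fair, but expedited notice would still need a belief in relatedness, and the board would still wait for the ruling.
- **The two rules on harm have different triggers.** A reader might infer that one IRB ruling sets off two incompatible instructions. That goes too far. Section {11b} concerns the therapy harming participants; section {22} concerns one event from any study procedure, which could be an interview or a hair sample. Discussing modifications also does not direct that the trial continue. What stands is that the relation between the sections is undefined where the harm is attributed to CTSP.
- **Who assesses relatedness.** A reader might infer that the PI both supervises the therapists and assesses relatedness. The section on training and supervision gives the PI a training role but does not say who provides the ongoing supervision, and section {22} does not say who forms the opinion on relatedness. The ruling on causality is the IRB's, an outside check. The point does not depend on the PI's role.
- **An article condenses.** Notification detail often sits in a full protocol or monitoring plan. Here, however, the article states the sequence and its conditions, so the point concerns a stated rule, not an omission.

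**Conclusion.** The point holds for the interval between routine board meetings. Section {22} gives the board a timed, event-driven notice only after three conditions are met: the event is unanticipated, it is believed related, and it is ruled a direct result of study procedures. A serious suicidal event judged expected or unrelated waits for the next meeting, although the board has the between-arm safety task and no interim analyses are planned.

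The wait is at most six months, in which up to 48 more youth could be randomised. A reader might take 48 as the typical figure; it is the upper bound, for an event just after a meeting, and the average is about 24 under uniform timing. Both assume recruitment at the planned rate. They measure exposure while the board is uninformed, not harm, because the article gives no event rate.

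The relation between section {11b} and sections {21a} and {22} is a separate point to reconcile. This review takes no view on which rule is right. The whole is a change the sponsor should make; it does not undermine the trial's design.

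**What to change.** In section {22}, send every death, life-threatening event and hospitalisation, with the assigned arm, to the board on the 48-hour clock already used for the IRB and NIDA. Do this whether or not the event is judged expected or related, and without waiting for the IRB's ruling. For this purpose the list should not depend on the section's definition of an adverse event, which would otherwise bring the expectedness filter back. Record the relatedness opinion, but do not use it as a gate.

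Reconcile section {11b} with sections {21a} and {22}, so that where harm is attributed to CTSP the text says which provision governs and which body decides. The choice is the sponsor's.

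The cost is protocol wording and extra notices to a three-member board, many of them uninformative singly. The background section expects attempts to be infrequent over the 12-month study period, so the load should be small.
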